### Who will be included in each analysis {27b}

The analysis populations will be defined as follows:Safety analysis set: All registered participants who received at least one dose of the study drug.Full analysis set (FAS): All registered participants who received at least one dose of the study drug, excluding those with major protocol violations (e.g., eligibility criteria violations, failure to obtain consent, non-registration, or other significant procedural errors).Per-protocol set (PPS): Participants in the FAS who strictly adhered to the 3-day intervention protocol and had complete data on the primary outcome.

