## Intervention and comparator

### Intervention and comparator description {15a}

The intervention period will be 3 days. The detailed protocols for the study medications are summarized in Table 1 and Fig. 1.

**Table 1 Tab1:** Protocol for study medications in the Active and Passive PBPM groups

Group	Route	Scheduled medication(19:00)	Action on insomnia
Active PBPM	Oral	**Ramelteon** 8 mg + **lemborexant** 5 mg	Additional **lemborexant** 5 mg (if insomnia persists)
	Non-oral	**Blonanserin** **patch** 20 mg (19:00–06:00)	**Hydroxyzine** (rescue)
Passive PBPM	Oral	None	1. **Ramelteon** 8 mg + **lemborexant** 5 mg 2. Additional **lemborexant** 5 mg (if insomnia persists) (Switch to regular **ramelteon** from next day)
	Non-oral	None	**Hydroxyzine** (rescue)

Intervention period: The protocol-based intervention will be performed for 3 consecutive days from the date of enrollment (day 1 to day 3). Active PBPM group: Pharmacists will actively intervene to initiate prophylactic medications, regardless of the presence of symptoms. Passive PBPM group: Medications will be administered only as symptomatic treatment if insomnia or delirium symptoms are observed. Regular administration in the Passive group: If rescue medication is required for insomnia in the oral intake group, Ramelteon 8 mg will be switched to regular administration at 19:00 from the following day.・Blonanserin patch: In the Active PBPM (non-oral) group, the patch will be applied for 11 h (from 19:00 to 06:00 the following morning)

*Abbreviations*: *PBPM* Protocol-Based Pharmacotherapy Management; *eGFR* estimated glomerular filtration rate

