**Fig. 1 Fig1:**
[figure not shown]
Detailed intervention and assessment schedules by enrollment timing. The timeline varies depending on the timing of enrollment. **A **Standard schedule: Enrollment on day 1 (08:30–17:00), with the 72-h protocol period starting that night. **B **Delayed schedule: Enrollment on day 2 for patients admitted at night or outside regular hours. The gray bar represents the 72-h protocol period. Blue squares indicate medication administration at 19:00 (Active group only). Green triangles indicate twice-daily nurse assessments using the DRS-R98-J at 20:00 and 10:00 (6 assessments total). The red star indicates the final diagnosis of the primary outcome by a blinded psychiatrist using DSM-5 criteria, performed within 3 days after protocol completion

Active PBPM group: Pharmacists will screen for delirium-inducing drugs upon admission. The patients will receive prophylactic medications for three consecutive nights.Oral intake possible: Ramelteon and lemborexant daily at 19:00.Oral intake impossible: The blonanserin patch will be applied daily from 19:00 to 06:00.Passive PBPM group: No prophylactic medications will be administered. Medications will be provided as rescue therapy only if insomnia occurs, following standard care procedures (Table 1).

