### Plans to promote participant retention and complete follow-up {25b}

Given the acute nature of the setting and the short follow-up period (72 h), high participant retention is expected. To ensure complete follow-up and minimize bias, the following strategies will be employed:

Retention Strategies: The PBPM intervention and assessments will be integrated into the standard clinical workflow of the emergency ward to minimize the burden on participants. Investigators and ward staff will monitor the participants’ clinical status daily to ensure adherence to the protocol.Data Collection for Discontinued Participants: If a participant deviates from or discontinues the intervention protocol (e.g., due to medical necessity, adverse events, or transfer to another ward), every effort will be made to continue the outcome assessments until the 72-h endpoint, provided that consent is not withdrawn.Outcome Data for Deviations: For participants who discontinue the study, the following data will be collected up to the point of discontinuation and included in the intention-to-treat (ITT) analysis:DRS-R98-JIncidence of agitation and medication recordsFinal delirium diagnosis by a psychiatrist (if possible, based on records up to the time of discontinuation)Withdrawal of Consent: If consent is withdrawn by the participant or their representative, all further data collection will cease. Data collected up to that point will be handled in accordance with the ethical approval and the participant’s preference.

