## Statistical methods

### Statistical methods for primary and secondary outcomes {27a}

The primary analysis will be performed on the FAS and repeated on the PPS as a sensitivity analysis. The incidence of delirium diagnosed using the DSM-5 within 3 days will be calculated for each group, with 95% confidence intervals (CIs). The between-group difference in incidence (Active PBPM minus Passive PBPM) and its 95% CI will be estimated using Newcombe’s method. Statistical significance will be set at a two-sided level of 5%. If the upper limit of the 95% CI for the difference is <0, the Active PBPM group will be considered to have a significantly lower incidence of delirium.

Unless otherwise specified, following secondary analyses will use a two-sided significance level of 5% and 95% CIs.Time to delirium: The time from enrollment to the onset of delirium (DSM-5) will be analyzed using Kaplan–Meier curves, with observations censored at 72 h.Delirium severity and sleep–wake cycle: Summary statistics for the worst DRS-R98-J severity scores and item 1 (sleep–wake cycle disturbance) scores recorded while the patient was awake will be compared between groups.

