### Protocol amendments {31}

To ensure recruitment feasibility within the designated study period, the inclusion criteria and enrollment procedures were amended twice following study initiation. All changes were approved by the Institutional Review Board of Kyoto University Hospital.First Amendment (June 21, 2024, Version 4.0): Expansion of recruitment days. Initially, enrollment was restricted to patients admitted on weekdays (8:30–17:00). To improve the recruitment rate, this restriction was removed, allowing enrollment on weekends and public holidays within the same time window.Second Amendment (April 9, 2025; Version 5.0): Extension of the enrollment window. To accommodate patients admitted outside of regular working hours or at night, the enrollment window was expanded from the day of admission (day 1, until 17:00) to the following day (day 2, until 17:00). To maintain the integrity of the intervention, patients enrolled on day 2 will be excluded if they have already received any study medications (ramelteon, lemborexant, or blonanserin patch), rescue medications (hydroxyzine), or antipsychotics before enrollment.

The target sample size remained unchanged following these amendments.

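### The full analysis set and safety set require a dose of study drug, but the Passive arm is dosed only on symptoms, so symptom-free Passive patients leave the primary comparison

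*Protocol article*

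**What the plan says.** In the protocol article, Statistical methods {27a} states: "The primary analysis will be performed on the FAS and repeated on the PPS as a sensitivity analysis". Section {27b} then defines three sets.

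- Full analysis set (FAS): "Full analysis set (FAS): All registered participants who received at least one dose of the study drug, excluding those with major protocol violations". The listed violations end with an open-ended category of procedural errors.
- Safety set: "Safety analysis set: All registered participants who received at least one dose of the study drug".
- Per-protocol set (PPS): a subset of the FAS.

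None of these definitions has arm-specific wording.

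Section {15a} treats the arms very differently. For Active: "Pharmacists will actively intervene to initiate prophylactic medications, regardless of the presence of symptoms". For Passive, the notes to Table 1 say: "Medications will be administered only as symptomatic treatment if insomnia or delirium symptoms are observed". The text below Fig. 1 gives insomnia as the only trigger: "No prophylactic medications will be administered. Medications will be provided as rescue therapy only if insomnia occurs". The Fig. 4 legend also names insomnia alone.

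Two other places bear on the point. Section {25b} says that data from participants who discontinue will be "included in the intention-to-treat (ITT) analysis", a set that {27b} does not define. Section {31}, on who may not be enrolled on day 2, lists "study medications (ramelteon, lemborexant, or blonanserin patch), rescue medications (hydroxyzine), or antipsychotics before enrollment", which places hydroxyzine outside the study medications. Table 1, whose title covers study medications in both groups, lists hydroxyzine as the only drug for Passive non-oral patients.

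**The concern.** A one-dose condition does little harm where every arm has scheduled treatment, because it removes few patients and for similar reasons in each arm. Here one arm is defined by having no scheduled drug. The condition keeps almost all Active patients, but keeps a Passive patient only after insomnia or delirium symptoms have led to treatment. Disturbed sleep is itself scored by item 1 of the DRS-R98-J, which is a secondary outcome and part of the material the psychiatrist uses for the diagnosis.

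Three things are at stake. The two arms of the primary analysis would no longer be the groups that were randomised. The PPS analysis, offered as the sensitivity check, would inherit the problem. The safety comparison, including falls and oversedation, would lose its unmedicated comparator patients. The sample size in {19} allows for 10% dropout and nothing for this exclusion.

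**Working it through.** **Inputs from the protocol.** Delirium 25% Passive and 5% Active; 80% power; two-sided 5%; 96 patients before dropout, so 48 per arm at 1:1 ({19}, {21b}). Active is declared better if the upper limit of the Newcombe 95% CI for Active minus Passive is below 0 ({27a}).

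**Assumed, because the protocol gives no figure.** a = share of delirious Passive patients who are dosed; b = share of non-delirious Passive patients who are dosed. All Active patients are taken as dosed.

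**Step 1: reproduce the plan.** With Wilson limits l and u for each arm, the upper limit is (pA − pP) + √[(uA − pA)² + (pP − lP)²]. Exact binomial enumeration of the rule that this upper limit be below 0, at 25% versus 5%, gives 79.3% power with 47 per arm and just over 80% with 48. The stated 96 therefore reproduces. With 25% in both arms and all 48 per arm analysed, the chance of declaring Active better is 2.5%, as intended.

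**Step 2: apply the one-dose rule with no true effect.** Let D = 0.25 in both arms.

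- Share of Passive entering the FAS: s = D·a + (1 − D)·b
- Delirium rate among them: r = D·a / s
- Apparent difference, Active minus Passive: D − r

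For a = 0.8 and b = 0.5: s = 0.25×0.8 + 0.75×0.5 = 0.575, so about 28 of 48 remain; r = 0.200/0.575 = 34.8%; the difference is −9.8 points. The last column below repeats the Step 1 enumeration, averaged over the binomial number of dosed Passive patients.

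| a (delirious) | b (not delirious) | Passive in FAS | Passive rate | Difference (points) | Active falsely declared better |
|---|---|---|---|---|---|
| 1.0 | 0.3 | 23 of 48 | 52.6% | −27.6 | 64% |
| 1.0 | 0.5 | 30 of 48 | 40.0% | −15.0 | 30% |
| 0.8 | 0.5 | 28 of 48 | 34.8% | −9.8 | 16% |
| 0.6 | 0.5 | 25 of 48 | 28.6% | −3.6 | 6% |
| 0.8 | 0.8 | 38 of 48 | 25.0% | 0 | 2.6% |
| 0.6 | 0.8 | 36 of 48 | 20.0% | +5.0 | 0.6% |

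The bias favours Active when a exceeds b, vanishes when they are equal, and reverses when a is below b.

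**Step 3: loss of power without selection on risk.** If dosing is unrelated to delirium, the Passive denominator still shrinks. At 25% versus 5%, power is 75% if 70% of Passive patients are dosed, 68% if 50% are (about 24 patients), and 57% if 30% are.

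**Step 4: non-oral patients.** If hydroxyzine is not study drug, as the list in {31} implies, a Passive patient who stays non-oral does not qualify through the Table 1 treatment. If hydroxyzine is study drug, as the Table 1 title implies, that patient qualifies once rescued. The protocol does not settle which reading applies.

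**The case against.** The strongest defence is that the wording was carried over from an ordinary drug trial and nobody intends to drop untreated Passive patients. Section {25b} speaks of intention to treat, and {19} sizes the trial on everyone less 10% dropout. That may well be the intention. It does not rescue the definition: no section counts Passive management as receiving study drug, and {5} says that the detailed analysis plan is integrated in this protocol, so {27b} is the operative rule.

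Four stronger readings are tempting, and the protocol does not support them.

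- *The bias certainly favours Active.* This is an inference. It is the expected direction, because Passive dosing follows symptoms close to the outcome. It would vanish or reverse if delirious Passive patients were dosed no more often than the others, for example if many had hypoactive delirium and went unmedicated.
- *No Passive non-oral patient can enter the FAS.* This rests on an enrolment bar in {31}, and the title of Table 1 points the other way. The effect on bias is also unclear. Section {19} cites nil-per-os patients as the reason for the higher baseline rate, so losing them from Passive alone would pull against Active. As an illustration, take 20.5% (a prior-study rate in {19}) as the oral risk, 70% oral, half of the oral patients with insomnia, and a risk ratio of 2 to 3 for insomnia. About 48 × 0.7 × 0.5 = 17 Passive patients remain. Their rate is 2×0.205/1.5 = 27.3% to 3×0.205/2 = 30.8%, and the false-claim rate against 25% in Active is about 4% to 8%.
- *Unblinded staff decide the violation exclusions.* No section says who decides. What stands is that the category is open-ended and applied after randomisation in an open-label trial.
- *Section {25b} calls the FAS analysis intention-to-treat.* It names such an analysis without equating it to the FAS. What stands is that the term is undefined in {27b}.

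**Conclusion.** The point stands as an error in the stated analysis sets and should be corrected before analysis. That the one-dose rule removes symptom-free Passive patients from all three sets follows from the text alone and needs no assumption; so does the loss of comparability by randomisation.

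The size does rest on assumptions: 48 randomised per arm, 25% true risk in both, all Active patients dosed, and dosing shares that the protocol does not give. Where delirious Passive patients are dosed more often than the others, the false-claim rate in the cases shown runs from 6% to 64%; the two middle cases give 16% and 30%. With dosing unrelated to delirium it stays at about the nominal 2.5%, and with the opposite pattern it falls below that. These figures show what the rule could do; they do not predict this trial's bias. The planned sample size of 96 is not in dispute.

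**What to change.** 1. Define the FAS as all randomised participants with valid consent, analysed in the allocated arm whether or not any drug was given.
2. Confine protocol-violation exclusions to the PPS. The only exception should be ineligibility on facts that predate randomisation, judged blind to arm and outcome. Delete the open-ended procedural category from the FAS definition.
3. Define the PPS so that a Passive patient who followed the protocol without needing drug counts as adherent.
4. Define the safety set by start of the allocated strategy, not by a dose.
5. Make {25b}, {27a} and {27b} name the same primary set, and state whether hydroxyzine is a study drug or a rescue drug wherever that term decides who is analysed. Reconcile the two descriptions in {15a} of what triggers Passive medication.

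The cost is wording, with the amendment and registry update that {5} already provides for. No new data are needed: the assessments are scheduled in both arms, and {25b} already plans outcome collection to 72 h after discontinuation unless consent is withdrawn. The article describes recruitment as ongoing, so the change should be made and dated before any comparative data are examined.

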### Eligibility criteria for participants {14a}

Patients will be eligible if they meet all the following inclusion criteria:Admitted to the general ward of the Department of Primary Care and Emergency Medicine via the emergency departmentAge ≥ 65 yearsPresent with at least one of the following six delirium risk factors, based on the Japanese national medical reimbursement criteria (“Delirium High-Risk Patient Management Addition”). Importantly, these factors are consistent with the established predisposing factors identified in major epidemiological studies [3, 16] and with international standards (e.g., American Geriatrics Society Beers Criteria) [17]:Central nervous system diseases (e.g., cerebrovascular disease, traumatic brain injury)Cognitive dysfunctionHistory of high alcohol intake (defined as ≥4 days/week)History of deliriumCurrent use of delirium-inducing drugs (e.g., benzodiazepines, corticosteroids, opioids, H2-receptor antagonists, psychotropics, anti-parkinsonian agents, or anticholinergics)Post-surgery or scheduled surgery requiring general anesthesia

Patients will be excluded if they meet any of the following criteria:SchizophreniaTaking antipsychoticsUnable to be hospitalized for >48 hTaking benzodiazepines prescribed by a psychiatrist or psychosomatic physicianTaking CYP3A4 inhibitors (e.g., itraconazole, clarithromycin, erythromycin, fluconazole, verapamil, human immunodeficiency virus protease inhibitors)Taking ramelteon or lemborexantBlonanserin patch is already appliedSevere liver dysfunctionSevere disturbance of consciousnessSedatives are used before the start of the studyDrug abuse

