### Criteria for discontinuing or modifying allocated intervention/comparator {15b}

Interventions will be discontinued in case of (1) intolerable adverse events, (2) use of prohibited medications, (3) withdrawal of consent, (4) post-enrollment discovery of ineligibility, or (5) significant clinical deterioration or death. No interim analysis is planned for this study. As such, no formal stopping rules for the entire trial have been established based on efficacy or futility. However, the principal investigator may terminate the trial early if unforeseen safety concerns arise.

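### The primary analysis set drops patients after randomisation for eligibility violations and an open-ended class of procedural errors, and this conflicts with the intention-to-treat wording in {25b}

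*Protocol article*

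**What the plan says.** Section {27a}: "The primary analysis will be performed on the FAS and repeated on the PPS as a sensitivity analysis".

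Section {27b} builds the FAS from registered participants who took at least one dose, "excluding those with major protocol violations (e.g., eligibility criteria violations"; the list goes on to missing consent, non-registration and a general class of other significant errors of procedure. The per-protocol set is then drawn from within the FAS.

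Section {15b} lists among the reasons for stopping the allocated intervention "4) post-enrollment discovery of ineligibility".

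Section {25b} says that every effort will be made to carry outcome assessment on to 72 h after the intervention is discontinued, unless consent is withdrawn. For those who discontinue the study it says that "the following data will be collected up to the point of discontinuation and included in the intention-to-treat (ITT) analysis".

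Sections {24a} and {24b} state that patients, ward physicians, pharmacists and nurses know the allocation, and that the diagnosing psychiatrists do not. Section {5} states that the detailed analysis plan is contained in this document under {27}.

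**The concern.** Randomisation protects the primary comparison only while the patients analysed are those randomised, or while removals cannot depend on arm or outcome. The FAS rule gives neither assurance. Removing patients without consent or registration is unobjectionable. Removing patients for an eligibility violation, or for a procedural error judged significant, is a decision that can be taken after the arm and the clinical course are known.

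Some criteria leave room for such judgement. One exclusion concerns patients who cannot stay in hospital beyond 48 h, and an early discharge could later be read as a breach of it. Another concerns sedatives used before the study starts, with no agents or time window given. The last item on the violation list has no boundary at all.

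Two things make this more than a matter of labels. No planned efficacy analysis would show the effect of the exclusions: the per-protocol set inherits them, and the worst-case imputation in {27c} deals with missing outcomes, not with patients left out of the set. Also, {25b} and {27b} give different instructions for the same patient. This is separate from the one-dose condition in the FAS definition, and would remain if every randomised patient counted as dosed.

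**Working it through.** **1. The two rules side by side.** Take a patient who is randomised, treated, and then found ineligible.
- {15b} item 4: the allocated intervention stops.
- {25b}: assessment continues to 72 h if possible, and the data of those who discontinue the study enter an intention-to-treat analysis.
- {27b}: the patient is an eligibility violation and leaves the FAS, and therefore the per-protocol set. No intention-to-treat set is defined.
- Result: the outcome is collected, but no efficacy analysis defined in {27b} uses it.

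Patients who stop for an adverse event, transfer or deterioration are not removed from the FAS on that ground. The conflict therefore concerns mainly item 4.

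**2. The plan's own sample size.** Inputs from {19} and {27a}: 25% Passive, 5% Active, two-sided 5%, 80% power, success if the upper 95% Newcombe limit for Active minus Passive is below 0. Exact binomial enumeration of that rule, without continuity correction, gives power 79.3% at 47 per arm and 80.3% at 48. So 2 × 48 = 96, as stated.

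Expected events: 48 × 0.05 + 48 × 0.25 = 2.4 + 12 = 14.4.

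**3. One exclusion in borderline data.** With p1 and p2 the Active and Passive proportions, u1 the Wilson upper limit for Active and l2 the Wilson lower limit for Passive, the upper Newcombe limit is

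(p1 − p2) + √[(u1 − p1)² + (p2 − l2)²].

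- 4/48 v 11/48: p1 = 0.0833, u1 = 0.1955, p2 = 0.2292, l2 = 0.1331. Upper limit = −0.1458 + √(0.1122² + 0.0961²) = −0.1458 + 0.1477 = +0.002. Interval −29.1% to +0.2%, not significant.
- 3/47 v 11/48: p1 = 0.0638, u1 = 0.1716. Upper limit = −0.1653 + √(0.1078² + 0.0961²) = −0.1653 + 0.1444 = −0.021. Interval −30.8% to −2.1%, significant.

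**4. How often the data lie there.** I summed the binomial probabilities of all outcomes at 48 per arm that are not significant as observed but become significant when one Active delirium case is removed. The result is about 9% at the planned 5% v 25%, and about 2.5% if both arms have a 15% rate. At roughly the planned expectation, 2/48 v 12/48, the upper limit is −6.8%. With one Active case removed (1/47) it is −9.4%, so the conclusion stands either way.

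**5. False-positive risk under assumed selective removal.** No true effect, 48 per arm, k delirium cases removed from the Active arm only. Chance of declaring Active better:

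| Rate in both arms | k = 0 | k = 1 | k = 2 | k = 3 |
|---|---|---|---|---|
| 25% | 2.5% | 4.0% | 6.6% | 9.7% |
| 15% | 2.1% | 4.6% | 9.3% | 15.4% |

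**6. Even-handed removal.** If about 5% or 10% of each arm is removed regardless of outcome (46 or 43 per arm), power goes from 80.3% to 78.1% or 75.9%. The loss is modest, so the issue is selective removal rather than numbers.

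**The case against.** The case against has four parts, each answering a stronger reading that the text may invite.

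- **That unblinded staff make the exclusions.** The protocol does not say so. It names nobody who classifies violations. Section {26} describes data management and monitoring as independent of the execution team, without stating whether they are blinded. The procedure for classifying violations may be in the full protocol. This part stands. What remains is that the rule as written carries no restriction to pre-randomisation facts and no blinding requirement.

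- **That drug histories are searched harder in the Active arm.** Section {15a} does say "Active PBPM group: Pharmacists will screen for delirium-inducing drugs upon admission". But {12} gives medication review at admission to pharmacists without restriction by arm, {20} has them screen all new admissions, {21b} uses baseline high-risk drug use as an allocation factor, and {23} confirms eligibility before the seal is opened. The documents do not support a difference between arms.

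- **That the eligibility criteria cancel each other.** The undefined sedative exclusion sits awkwardly beside benzodiazepine use and "Post-surgery or scheduled surgery requiring general anesthesia" as qualifying risk factors. But the list separately excludes benzodiazepines prescribed by a psychiatrist or psychosomatic physician, which would be redundant if every benzodiazepine counted as a sedative. Several listed risk drugs are not sedatives, and scheduled surgery need not involve any prior anaesthetic. This is loose wording to reconcile, not a contradiction that empties the criteria.

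- **That one patient reverses the trial.** The 4 v 11 example is a chosen boundary case. At the planned expectation, one removal changes nothing. This stands, and is why step 4 gives a probability.

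Deferral to a separate analysis plan does not answer the main point, because {5} says the plan is in this text and {27b} is a stated rule.

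**Conclusion.** The point holds in a limited form. The primary set removes treated patients after randomisation on grounds that include eligibility and an unbounded procedural category. No planned efficacy analysis recovers them, and "included in the intention-to-treat (ITT) analysis" in {25b} cannot be squared with {27b} for patients later found ineligible.

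The size is conditional. With about 14 expected events, removing one Active delirium case would turn a non-significant result significant in about 9% of trials at the planned rates, and in about 2.5% if both arms have a 15% rate. These figures assume 48 evaluable patients per arm and that the removed patient is an Active case. The protocol gives no expected number of exclusions, so the false-positive figures for one to three removals are illustrations, not predictions. Nothing in the documents shows that selective removal will occur; the text simply does not prevent it. It should be corrected before analysis.

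**What to change.** - **{27b}:** define the primary set as every validly consented randomised patient, analysed as randomised. Move eligibility violations and procedural errors to the per-protocol definition. This definition would also replace the one-dose condition.
- **{25b}:** use the name of that set in place of the undefined intention-to-treat analysis, and make clear that patients found ineligible after randomisation are still assessed to 72 h, unless consent is withdrawn, and are analysed.
- **{14a}, secondary:** reconcile the sedative exclusion with the benzodiazepine and post-surgery risk factors. How the criterion should read is for the investigators to decide.

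The cost is an amendment to wording. The planned 96 evaluable patients do not change. The downside is that a few ineligible patients stay in the primary comparison and may dilute the effect slightly; the per-protocol analysis will show the result without them.

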### Concomitant care permitted or prohibited during the trial {15d}

#### Standard care and concomitant management

All participants will receive standard non-pharmacological delirium prevention, including cognitive orientation, dehydration prevention, early mobilization, and sleep hygiene.Rescue medications: If agitation develops, rescue medications (e.g., intravenous hydroxyzine or haloperidol) will be administered according to a standardized treatment algorithm (Fig. 2).Prohibited medications: Concomitant use of other antipsychotics or hypnotics will be strictly prohibited during the study period.Adverse events: Any adverse events will be managed with appropriate supportive care. Detailed procedures for the systematic collection and classification of harms are described in the Harms {17} section. The participants will be covered by the clinical trial insurance.

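### The per-protocol set judges adherence beyond delirium onset, so patients in either arm can be excluded because of the outcome, and the set is not a neutral check on the primary result

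*Protocol article*

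**What the plan says.** Section {27a} of the protocol article gives the PPS its role: "The primary analysis will be performed on the FAS and repeated on the PPS as a sensitivity analysis". Section {27b} defines it: "Participants in the FAS who strictly adhered to the 3-day intervention protocol and had complete data on the primary outcome". The definition does not say what adherence means in each arm, and adherence does not stop being judged when delirium starts. The PPS is drawn from the full analysis set (FAS), which is itself restricted: "All registered participants who received at least one dose of the study drug, excluding those with major protocol violations".

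What there is to adhere to differs by arm. In {15a}, the text under Fig. 1 says of Active: "The patients will receive prophylactic medications for three consecutive nights". Of Passive it says: "No prophylactic medications will be administered". The notes to Table 1 add that, once a Passive oral patient has needed rescue medication for insomnia, "Ramelteon 8 mg will be switched to regular administration at 19:00 from the following day".

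Other ways of departing from the protocol apply to both arms. Section {15d} states: "Concomitant use of other antipsychotics or hypnotics will be strictly prohibited during the study period". Section {15b} lists "2) use of prohibited medications" and significant clinical deterioration among the reasons for discontinuing the allocated intervention or comparator. Section {25b} says that outcome assessment should continue to 72 h after a deviation, unless consent is withdrawn.

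**The concern.** The primary outcome can occur on the first or second night, while adherence is judged to the end of day 3. A patient who becomes delirious on night 1 and then refuses tablets, removes a patch, receives a prohibited drug or is discontinued for deterioration has not strictly adhered for three days. Under {27b} that patient leaves the PPS and the event goes too, even though {25b} means it may well have been recorded. Membership of the set can thus depend on the outcome that the set is meant to analyse.

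If this happens equally in both arms, both rates fall and little is lost beyond precision. If it happens unequally, the PPS difference moves for reasons unrelated to the drugs. Agreement between FAS and PPS would then reassure falsely, and a significant PPS result beside a neutral FAS result could be an artefact. This is not detail left to another document: section {5} says that the detailed analysis plan is integrated in this protocol.

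**Working it through.** **Inputs from the documents.** 25% delirium in Passive and 5% in Active, 80% power, two-sided 5%, Newcombe's method, 96 evaluable patients ({19}); 1:1 allocation ({21b}); success if the upper 95% limit of Active minus Passive is below 0 ({27a}).

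**The plan's own figure.** Enumerating all binomial outcomes at 5% v 25% and counting those with an upper Newcombe limit below 0 gives power of 79.3% at 47 per arm and just over 80% at 48. The stated 96 reproduces, so 48 per arm is used below.

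**Routes out of the PPS after delirium begins**

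| Route | Active | Passive |
|---|---|---|
| Missed scheduled dose | Every patient, three nights | Oral patients after insomnia rescue, on remaining nights |
| Prohibited medication | Yes | Yes |
| Discontinuation for deterioration | Yes | Yes |

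The first row is unequal. The other two are open to both arms.

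**Expected PPS rate.** Let p be the true delirium rate and q the share of delirious patients dropped, with all others kept. The PPS rate is p(1−q)/(1−pq). At p = 0.20:

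- q = 0.25: 0.15/0.95 = 15.8%
- q = 0.50: 0.10/0.90 = 11.1%

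The documents give no value for q, so every value here is an assumption.

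**Chance of a false Active win.** Events in each arm are Binomial(48, p), events kept are Binomial(events, 1−q), and the set size is 48 minus the events dropped. Exact enumeration with no true effect gives:

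| Active events lost | Passive events lost | p = 20% | p = 25% |
|---|---|---|---|
| 0 | 0 | 2.4% | 2.5% |
| 25% | 0 | 7.2% | 8.1% |
| 50% | 0 | 19.9% | 23.5% |
| 50% | 25% | 8.3% | 9.7% |
| 50% | 50% | 2.0% | 2.2% |

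**Losing non-delirious Active patients too.** With a share s of them dropped, the Active PPS rate is p(1−q)/[p(1−q) + (1−p)(1−s)]. Simulation at p = 20%:

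- q = 0.50, s = 0.20: 0.10/(0.10 + 0.64) = 13.5%; false Active win about 10%.
- q = 0.25, s = 0.10: 0.15/(0.15 + 0.72) = 17.2%; about 5%.
- The same, with a quarter of Passive events also lost: 17.2% v 15.8%; about 1.5%, and the tilt is now against Active.

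**Worked case.** The Newcombe upper limit is d + √[(u_A − p_A)² + (p_P − l_P)²], where u and l are Wilson limits.

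- FAS 6/48 v 12/48: d = −12.5 points; u_A = 0.247, l_P = 0.149; 95% CI −27.8 to +3.3, not significant.
- Three delirious Active patients dropped, 3/45 v 12/48: d = −18.3 points; u_A = 0.179; CI −32.8 to −3.3, significant.
- Three delirious Passive patients dropped as well, 3/45 v 9/45: d = −13.3 points; l_P = 0.109; CI −27.8 to +1.1, not significant.

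**The case against.** A reader might infer that only Active patients can fail by missing a dose, that Passive patients have no matching route, and that the PPS therefore must tilt towards Active. The documents do not support this. A rescued Passive oral patient acquires a regular 19:00 dose that can be missed. The prohibited-medication and deterioration rules cover both arms. Read literally, the FAS dose condition also keeps never-dosed Passive patients out of the PPS, so the Passive patient with nothing to adhere to is not in the comparison. Nor do the documents say that delirium causes missed doses. These points stand, and they remove any claim of a fixed direction.

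It can also be said that the FAS is primary, that no stated rule lets the PPS override it, and that selection on adherence is a general weakness of per-protocol sets. This limits the consequence but does not remove it: {27a} offers the PPS as the check on the primary result, and the avoidable part of the weakness is counting adherence after the event.

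The prohibited-medication route in Passive may be narrower than it looks. Section {15d} provides rescue for agitation, with haloperidol as an example, under a standardized algorithm, and a patient treated that way would seem to be following the protocol. The article does not say how such use counts for the PPS.

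**Conclusion.** The point holds in a limited form. Strict three-day adherence with no cut-off at delirium onset opens the PPS to outcome-dependent selection in both arms. The heavier Active dosing schedule makes a tilt towards Active plausible but not certain, and larger Passive losses would reverse it. Either way the PPS is not a neutral sensitivity check.

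The size depends on loss shares that the documents do not give. The 7% and 20% figures assume that no Passive events and no non-delirious Active patients are lost; relaxing either assumption brings them down, to about 2% when event losses are equal. All figures also take 48 per arm into the FAS, which a literal reading of the dose condition may not deliver in Passive. That condition is a separate matter. The primary FAS analysis is not affected by this point, so the change should be made but is not critical.

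**What to change.** In {27b}, state what adherence means in each arm, including how rescue under the agitation algorithm counts, and judge it only up to the first of delirium onset, death, discharge or 72 h. A patient who followed the allocated protocol until delirium began stays in the PPS with the event counted. In {27a}, call the PPS analysis supplementary and report the number excluded by arm and delirium status.

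The cost is a sentence or two in {27b}, a change of label in {27a} and one table row. No new data are needed: onset time is already required for the time-to-delirium outcome. One small downside is that the psychiatric diagnosis is made between day 4 and day 7, so onset is assigned retrospectively from records, as it already must be for that outcome. The change removes exclusions that follow onset; the table row shows any imbalance that remains.
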